### Participants

Participants will be recruited from children who have undergone ERCP in the pediatric department of Shanghai Shuguang Hospital. Inclusion criteria are as follows: (1) aged between 2 and 12 years, (2) having completed ERCP, (3) deemed suitable for pediatric acupressure and external mirabilite application, (4) having provided written informed consent by legal guardians, and (5) having provided age-appropriate assent from the child. Exclusion criteria are as follows: (1) history of abdominal surgery or severe gastrointestinal dysmotility; (2) concomitant failure of vital organs, such as the heart, lung, or kidney; (3) known allergy to mirabilite or skin lesions contraindicating topical application; (4) cognitive or behavioral impairment that would compromise cooperation with acupressure; and (5) intraoperative conversion to open surgery due to major complications, such as perforation or severe bleeding. Participants will be withdrawn under the following circumstances: (1) voluntary withdrawal by the child or their parent; (2) loss of communication during the intervention that precludes further assessment; or (3) the occurrence of a serious adverse event, including marked clinical deterioration or an acute medical condition.

Eligible children will be identified through an electronic medical record system, with 2 senior physicians independently evaluating their enrollment criteria. In the event of disagreement, a third expert will adjudicate. All participants will have the research protocol thoroughly explained by a dedicated research nurse before surgery, and informed consent will be obtained from the guardians and the children.

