### Sample Size

G*Power (version 3.1; Heinrich Heine University Düsseldorf) software was used to calculate the sample size. We used the *F* test as the method for statistical analysis, establishing an α of .05 and a power (1–β) of .95. The estimation was based on data from a previous high-quality clinical trial, which used a 3-arm parallel design evaluating combined mirabilite application with massage, massage alone, and mirabilite application alone in patients undergoing laparoscopic hepatectomy [23]. Using the reported group means, a pooled SD of 13.03 hours, and a sample size of 30 per group from that trial, the software estimated an effect size (*f*) of 0.593. On the basis of this effect size, the calculated total sample size required for this 4-group study was 56 participants. To account for an anticipated dropout rate of 20%, the final planned total sample size is 72 participants, with approximately 18 (25%) individuals allocated to each group.

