#### Secondary Outcomes

##### Overview

To comprehensively evaluate postoperative recovery and investigate potential mechanisms, the subsequently mentioned secondary outcomes will be monitored. The first outcome is the incidence of PONV. The frequency of PONV episodes will be recorded every 4 hours. The second outcome is postoperative inflammatory markers. To establish baseline values and track the perioperative inflammatory trajectory, venous blood samples for quantification of WBC count and serum amylase levels will be collected before surgery, at 3 hours after surgery, and on the morning of postoperative day 1. These parameters will serve to assess pancreatic functional recovery, screen for complications, and gauge the magnitude of the systemic inflammatory response. Furthermore, they will provide indirect indicators of gastrointestinal functional status, offering valuable reference data for monitoring postoperative clinical progression.

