### Data Analysis

Statistical analyses will be performed using SPSS (version 25.0; IBM Corp) and RStudio (Posit PBC), incorporating the *survival* package. A 2-sided significance level of .05 will be applied for all tests, and an intention-to-treat analysis will be implemented to handle missing data.

Categorical baseline variables will be summarized as frequencies and percentages, with group comparisons conducted using chi-square tests or Fisher exact tests as appropriate. Continuous variables will be described as mean with SD if normally distributed and compared via 1-way ANOVA; nonnormally distributed variables will be presented as median with IQR and compared using the Kruskal-Wallis *H* test. Time-to-event analysis will be applied to the primary outcomes, namely time to first flatus and time to first defecation. Cumulative event rates will be visualized using Kaplan-Meier curves, and overall, between-group differences will be assessed via the log-rank test. To address multiple comparisons, a prespecified hierarchical contrast approach will be used. Primary contrasts, including each intervention group compared to the routine care group, will be evaluated using a Bonferroni-adjusted significance threshold of .0167. Exploratory pairwise contrasts between the combination group and each monotherapy group will be conducted only if significant differences are observed in the primary contrasts. Additionally, a Cox proportional hazards regression model will be used to estimate adjusted hazard ratios with 95% CIs for each intervention relative to routine care while controlling for baseline covariates identified in univariable analysis with a *P* value of <.10.

The secondary outcome analysis will include comparisons of PONV incidence using chi-square tests, with Bonferroni-adjusted pairwise testing where applicable. Inflammatory markers, including WBC count and serum amylase, will be analyzed using repeated-measures ANOVA to evaluate changes at 3 hours after surgery and on the morning of postoperative day 1. Safety outcomes will be summarized descriptively, and between-group differences in adverse events will be examined using chi-square or Fisher exact tests.

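### WBC count and serum amylase are analysed by repeated-measures ANOVA that gives the pre-surgery value no covariate role; using it as a covariate is usually more efficient and needs no new data

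*Protocol article*

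**What the plan says.** Under Secondary Outcomes (Overview), blood for both markers "will be collected before surgery, at 3 hours after surgery, and on the morning of postoperative day 1". The stated purpose of the series is "To establish baseline values and track the perioperative inflammatory trajectory". Table 1 also marks a baseline value for each marker.

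Under Data Analysis, the markers "will be analyzed using repeated-measures ANOVA to evaluate changes at 3 hours after surgery and on the morning of postoperative day 1". Only the two post-surgery times are named. The text does not say whether the pre-surgery value is a third time level or is left out, or whether the group effect or the group-by-time term is the test. The only covariate adjustment named is in the Cox model for the primary outcomes, "while controlling for baseline covariates identified in univariable analysis with a *P* value of <.10".

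The pre-surgery sample precedes allocation: one inclusion criterion is "having completed ERCP", and Table 1 places randomization after surgery. It is therefore a valid baseline covariate.

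**The concern.** A baseline value is collected from each child and the named analysis does not use it in the way that gives most precision. As a third time level, it makes the group-by-time test compare changes from baseline, which carries the full noise of the pre-surgery value. Left out, stable differences between children remain in the error of the group effect.

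These are the trial's only laboratory outcomes, and the Discussion looks to biological indicators for preliminary evidence on mechanism, in particular an anti-inflammatory effect. The sample size was derived from a recovery time in hours, so nothing in the plan secures power for the markers. With about 18 children per arm, precision that costs nothing is worth having.

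**Working it through.** **The plan's own figure.** Sample Size uses a one-way ANOVA F test, "establishing an α of .05 and a power (1–β) of .95", f = 0.593 and 4 groups. With noncentrality N × f² and (3, N − 4) degrees of freedom, the smallest N reaching 0.95 is 53, or 56 in equal groups. Then 56 / 0.80 = 70, or 72 in equal groups. The figures reproduce, but they concern recovery time. No power is stated for WBC or amylase.

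**Inputs for the markers.** From the article: 4 arms, 72 children (18 per arm), one pre-surgery and two post-surgery values, and "A 2-sided significance level of .05 will be applied for all tests". Assumed, because the article gives neither: arm effects of 0, -0.5, -0.5 and -1.0 SD at both post-surgery times, and a common correlation ρ between any two times. The effects average -0.5, so f² = (0.25 + 0 + 0 + 0.25) / 4 = 0.125 and f = 0.354 per time point.

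**Error variances, SD = 1.**
- Group effect on the mean of the two post-surgery values: (1 + ρ)/2.
- The same with the pre-surgery value as covariate: (1 + ρ)/2 − ρ² = (1 − ρ)(1 + 2ρ)/2.
- Post-surgery mean minus pre-surgery value: (1 + ρ)/2 + 1 − 2ρ = 1.5(1 − ρ). This is also the variance behind the three-level group-by-time test, which is why that test is in effect a change-score analysis. It spends 6 numerator degrees of freedom instead of 3.

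**Power.** Noncentrality is 72 × 0.125 / variance = 9 / variance. Denominator degrees of freedom are 68, 67 and 136 in the order of the columns.

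| ρ | Variances | Group effect, no covariate | Group effect, covariate | Three-level group-by-time |
|---|---|---|---|---|
| 0.1 | 0.55, 0.54, 1.35 | 0.925 | 0.930 | 0.43 |
| 0.2 | 0.60, 0.56, 1.20 | 0.90 | 0.92 | 0.48 |
| 0.3 | 0.65, 0.56, 1.05 | 0.87 | 0.92 | 0.54 |
| 0.5 | 0.75, 0.50, 0.75 | 0.82 | 0.95 | 0.72 |
| 0.7 | 0.85, 0.36, 0.45 | 0.76 | 0.99 | 0.93 |

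Simulation of the same setting gave 0.88, 0.81 and 0.76 without the covariate, 0.92, 0.95 and 0.99 with it, and 0.55, 0.71 and 0.93 for group-by-time at ρ = 0.3, 0.5 and 0.7. This agrees with the formulas to within 0.01.

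**Relative efficiency of the covariate analysis.** Against the post-surgery-only group effect it is (1 + ρ) / [(1 − ρ)(1 + 2ρ)] = 1.16, 1.50 and 2.36 at ρ = 0.3, 0.5 and 0.7. Against the change score it is 3 / (1 + 2ρ) = 1.88, 1.50 and 1.25.

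**Sensitivity.**
- With 56 children, the N before dropout, the group effect moves from 0.76, 0.69 and 0.63 to 0.83, 0.87 and 0.96 at ρ = 0.3, 0.5 and 0.7.
- If the two post-surgery values correlate 0.7 but pre-post only 0.3, it moves from 0.76 to 0.81.
- Across the simulated settings, adding the covariate to the two post-surgery times never lost more than about 1 percentage point.

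**The case against.** **The stated method does not always lose.** A reader might infer that every form of repeated-measures ANOVA here is less efficient than ANCOVA. That is not so. Read literally, the plan has two time levels, and their group-by-time test uses the 3-hour value as each child's own control. If the whole effect appears on day 1, with pre-post correlation 0.3 and post-post 0.7, that test has variance 2(1 − 0.7) = 0.6 and power of about 0.90. ANCOVA of day 1 on the pre-surgery value has variance 1 − 0.09 = 0.91 and power of about 0.73 (simulated 0.89 against 0.71). Because surgery falls between the first two samples, such a pattern is plausible. This objection stands. It argues for keeping arm-by-time in the model, and it is no reason to omit the covariate.

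**Part of any apparent gap can come from the time point.** With an effect on day 1 only, averaging the two post-surgery times gives power of just 0.30, 0.26 and 0.23 at ρ = 0.3, 0.5 and 0.7, and still only 0.34, 0.38 and 0.51 with the covariate. Such low figures should not be charged to the missing covariate. The comparison under Working therefore holds the time points fixed.

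**The 3-hour comparison cannot be set aside.** A reader might infer from twice-daily delivery that at most one session can precede the 3-hour sample, and so make that comparison descriptive. The article gives no time for the first session, and it names both times for analysis. The inference is unsupported.

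**Model detail may sit in an analysis plan that is not shown.** This is fair for the exact terms, and the article does not rule out a covariate. But it does name the method, and the method as named gives the baseline value no such role. Repeated-measures ANOVA is valid and its type I error is not in question.

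**Conclusion.** The point holds as a loss of efficiency in two secondary outcomes. It is not a bias, not an inflated error rate and not an error of fact. Under the assumed effects at both post-surgery times with 18 per arm, the covariate raises power of the group test by about 4, 14 and 23 points at correlations of 0.3, 0.5 and 0.7. Against the three-level group-by-time test the gain is about 37, 24 and 6 points.

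The size rests on assumed effects, a normal model and an assumed correlation, none of which the article supplies. Against a post-surgery-only group test the gain is negligible at a pre-post correlation of about 0.1 and about 2 points at 0.2. Mixed indications suggest wide spread between children, but spread does not establish correlation across an intervening procedure.

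**What to change.** Replace the sentence on the markers under Data Analysis with:

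> WBC count and serum amylase at 3 hours and on the first postoperative morning will be analysed in a linear mixed model with arm, time, arm-by-time and the pre-surgery value (by time) as covariate; adjusted differences between each intervention arm and routine care will be reported at both times.

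Both planned time points stay, and so does the arm-by-time test. Name the covariate as the sample drawn before surgery, because Data Collection and Management describes baseline data as collected after allocation.

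The cost is one sentence and one degree of freedom per time point. No extra blood sample or change in procedure is needed. The article reports 38 children randomized as of January 2026 and no interim analysis, so on its account the change can still be specified before any data are analysed.

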**Conclusions:**

This study is the first to rigorously assess the efficacy and potential synergistic effects of acupoint massage and mirabilite application for enhancing gastrointestinal recovery after pediatric ERCP. Positive findings could establish a safe, nonpharmacological protocol to improve postoperative outcomes, reduce hospital stays, and minimize complications in this vulnerable population.

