### Study Aims

This study aims to comprehensively evaluate the effects of acupoint massage, the external application of mirabilite, and their combined intervention on gastrointestinal function recovery in children following ERCP procedures. The primary objectives include comparing the efficacy of the 3 interventions—acupoint massage, mirabilite application, and the combined approach—against a routine care group, specifically in terms of shortening the time to first postoperative flatus and bowel movement. Additionally, this study aims to clarify whether the combined intervention offers advantages over individual therapies to determine the optimal clinical strategy. The secondary objectives involve assessing the degree of improvement in postoperative symptoms, including PONV; analyzing changes in inflammatory markers, including serum amylase and WBC count; and verifying the safety of the interventions regarding issues such as skin irritation and procedural tolerance. This research not only determine the optimal strategy to address the existing evidence gap in accelerated recovery following pediatric ERCP but also provides a scalable, standardized protocol for rapid postoperative recovery in pediatric patients.

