## Methods

### Study Design

A parallel 4-group, single-blind, randomized controlled trial (RCT) will be conducted from November 1, 2024, to October 30, 2026. The study will take place in the pediatric department of Shuguang Hospital in Shanghai. After baseline assessments, eligible participants will be randomly assigned in a 1:1:1:1 ratio to 4 groups: acupoint massage group, mirabilite group, combination group, and conventional care group (Figure 1; Table 1). Table 2 presents the content and procedures used in each intervention group. The standardized intervention manual can be found in Multimedia Appendix 1. The primary outcome measure will be the time to postoperative gas passage or stool, whereas the secondary outcomes will include the incidence of PONV as well as changes in inflammatory markers. This study will adhere to the SPIRIT (Standard Protocol Items: Recommendations for Interventional Trials) guidelines (Multimedia Appendix 2) [22]. This protocol was registered at the International Traditional Medicine Clinical Trial Registry (ITMCTR2025000670) on April 7, 2025.

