The core innovation of this study is the introduction of a combined intervention model that uses acupoint massage to regulate organ Qi and enhance gastrointestinal motility, alongside the external application of mirabilite to alleviate swelling and promote bowel movements. This integrated approach aims to create a synergistic effect that comprehensively supports the recovery of gastrointestinal function.

This research uses a rigorous RCT design, systematically evaluating the effects of acupoint massage, external application of mirabilite, and their combined approach on the improvement of gastrointestinal function in children after ERCP, which clearly distinguishes the independent contributions of each intervention and their potential synergistic effects, thus providing a reliable basis for determining the optimal treatment strategy. Furthermore, this study aims to establish standardized operational parameters for acupoint massage and the external application of mirabilite for children, including acupoint selection, techniques, treatment frequency, and duration for external application, laying the groundwork for future clinical applications. The research pays attention to clinical end point and biological indicators, aiming to provide preliminary evidence on the mechanisms of action of the interventions, especially concerning their anti-inflammatory effects. Additionally, rigorously recorded safety data that meet expectations will become crucial for supporting clinical promotion. This study has significant advantages, as a noninvasive, nonpharmacological external treatment method; its high safety and ease of operation make it more acceptable to children and parents. Compared to mandatory early ambulation, this method is less painful, with low costs for mirabilite and controllable labor costs, providing good health economic value.

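### The plan sets out to verify safety, but a descriptive summary and difference tests on about 18 children per arm give no criterion that could support that conclusion

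*Protocol article*

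**What the plan says.** Study Aims lists, among the secondary objectives, "verifying the safety of the interventions regarding issues such as skin irritation and procedural tolerance". The analysis that serves it is one sentence in Data Analysis: safety outcomes get a descriptive summary, and "between-group differences in adverse events will be examined using chi-square or Fisher exact tests". The same section states that "A 2-sided significance level of .05 will be applied for all tests".

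On size, Study Design says that "eligible participants will be randomly assigned in a 1:1:1:1 ratio to 4 groups", and Sample Size that "the final planned total sample size is 72 participants, with approximately 18 (25%) individuals allocated to each group". That number comes from an F test on an efficacy effect size; safety plays no part in it.

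On what is to be concluded, the abstract's Conclusions say: "Positive findings could establish a safe, nonpharmacological protocol to improve postoperative outcomes". The Discussion adds that "rigorously recorded safety data that meet expectations will become crucial for supporting clinical promotion", without saying what the expectation is. Its closing summary also names a safe option for practice among the aims.

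Table 2, the Mirabilite Group section, and Quality Control and Precautions set monitoring and discontinuation rules for the individual child. They are not criteria for the trial's conclusion about safety.

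**The concern.** Verifying safety means showing that harm is no more frequent than some tolerable level. A chi-square or Fisher test asks another question: whether the data contradict equal event rates. Failing to contradict equality is weak evidence when arms are small, because sizeable imbalances remain compatible with chance. A descriptive summary shows the counts but does not say how large a true rate they leave open.

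At stake is the safety conclusion for children aged 2 to 12. The stated objective and the stated method do not meet, and nothing in the text tells the analyst or reader what result would count as verified.

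**Working it through.** **Inputs from the protocol article.** Four arms, 1:1:1:1 (Study Design); 72 children, about 18 per arm, f = 0.593, power .95, 20% dropout (Sample Size); two-sided .05, chi-square or Fisher (Data Analysis). Routine care receives neither massage nor mirabilite (Conventional Care Group), so a zero count there is realistic for application-site reactions and massage intolerance. No adverse-event rate is given anywhere.

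**1. The plan's own figure.** For a four-group F test the noncentrality is N × f². At N = 56 this is 56 × 0.593² = 19.7 and power is 0.962; at N = 52 power is 0.946. So 56 reproduces. Dropout: 56 / 0.80 = 70, rounded up to 4 × 18 = 72. The size is right for its purpose, which is efficacy only.

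**2. Fisher test, no events in routine care (no assumed rate needed).** With k events, all in one of two arms of 18, two-sided P = 2 × C(18,k) / C(36,k).
- k = 3 (17%): 2 × 816 / 7,140 = .229
- k = 4 (22%): 2 × 3,060 / 58,905 = .104
- k = 5 (28%): 2 × 8,568 / 376,992 = .045, the first significant count

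**3. Uncorrected chi-square on the same tables.** The statistic reduces to 36k / (36 − k).
- k = 3: 108 / 33 = 3.27, P = .070
- k = 4: 144 / 32 = 4.50, P = .034

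At k = 4 the expected number of events is only 2 per arm, where Fisher is the usual choice. At k = 3 both tests are non-significant.

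**4. What zero events would show.** The exact (Clopper-Pearson) two-sided 95% upper limit for 0/n is 1 − 0.025^(1/n).
- n = 18: 18.5%
- n = 36 (two arms sharing a component): 9.7%

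**5. Power, under assumed rates only.** Sum the product of the two binomial probabilities over all tables with P ≤ .05, 18 v 18:

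| Assumed rates | Fisher | Uncorrected chi-square |
|---|---|---|
| 1% v 5% | 0.1% | 0.9% |
| 2% v 10% | 2.0% | 7.0% |
| 5% v 25% | 24.7% | 39.3% |
| 10% v 50% | 66.8% | 78.5% |
| 15% v 75% | 95.9% | 98.3% |

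If the test is read as one overall four-group comparison, with both mirabilite arms at 25% and the other two at 5%, power is about 45% (exact) or 50% (chi-square), from 4,000 simulated trials.

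**The case against.** A descriptive summary plus Fisher tests is conventional for secondary safety data in a trial sized for efficacy, and low power for adverse events is nearly universal. Interval methods and rules for reading P values are commonly left to an analysis plan, which is not shown, and this is a condensed article. Skin reactions and massage intolerance can hardly occur in routine care, so for them the descriptive summary is the informative part. The Discussion also calls for larger multicenter trials to validate the results.

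Much of this stands. The absence of a named interval method would not be a finding by itself. The point survives because the article fixes both the objective and the method, and the two do not fit.

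Three stronger readings are tempting and are not supported:
- A reader might infer that a fivefold rise in events would be missed about 75% of the time. That holds only for an assumed 5% v 25% under a pairwise Fisher test. The table above shows fivefold rises missed from more than 99% of the time to about 4%, and the chi-square test that the plan also allows misses 61% at 5% v 25%.
- A reader might infer that a significance test is the only safety analysis. A descriptive summary is planned too, though it is not a decision criterion.
- A reader might infer that P>.05 will be reported as safe. No passage says so: the abstract's wording is conditional, and the analysis section says only that differences will be examined.

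Nor is a smaller number per arm after dropout used here. The analysis is by intention to treat, and withdrawal for distress or a serious adverse event is itself a safety observation.

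**Conclusion.** The point holds in a limited form. The objective of verifying safety is not matched by any criterion, and the stated difference tests cannot provide one at about 18 children per arm. The size can be given without an assumed event rate: 0/18 v 4/18 is non-significant by Fisher, 0/18 v 3/18 is non-significant by either test, and an arm with no events at all still leaves true rates up to 18.5% open (9.7% for 36 children). These figures rest on full arms of 18 and the two-sided .05 level. Power figures are illustrations only, because the documents give no adverse-event rates. The finding is a mismatch of method and aim; it is not evidence that the interventions are harmful or that the authors intend to misread a P value.

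**What to change.** In Data Analysis, base the safety objective on estimation:

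1. Report, per arm, the proportion of children with a skin reaction, with intolerance and with any adverse event, each with an exact (Clopper-Pearson) 95% confidence interval.
2. Optionally add the pooled arms exposed to each component (mirabilite plus combination; massage plus combination; about 36 each), with the combination arm also shown alone.
3. For events possible in every arm, give the risk difference against routine care with a 95% confidence interval.
4. State that a non-significant P value will not be read as evidence of safety, and that any safety statement will quote the upper 95% limit.

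In Study Aims, replace the aim of verifying safety with one of estimating the frequency of adverse events.

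The cost is a few intervals and some wording, with no extra patients, data or staff. The article reports 38 of 72 children randomized by January 2026 and no interim analysis, so the change can still be made before any results are known. The downside is a more modest claim. Pooling, if used, assumes that component-specific events occur similarly with and without the other component, which is why the combination arm should also stand alone.
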